## Abstract

**Aims:**

The concept of prehabilitation, defined as interventions aimed at enhancing a patient's functional capacity prior to an impending physiological stressor, may contribute to reduced postoperative morbidity and mortality. The study's goal is to verify or refute the feasibility of a prehabilitation programme for two diagnostic patient groups during neoadjuvant chemo(radio)therapy, which is prescribed before the scheduled surgical procedure. This is a single group study design, with all patients enrolled receiving the intervention.

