## Introduction

Curative treatment of the cancer of upper gastrointestinal tract (oesophagus, oesophago-gastric junction, and stomach) and treatment of rectal cancer is multimodal. Neoadjuvant chemotherapy, radiotherapy, or chemoradiotherapy (further referred to as neoadjuvant therapy) is commonly indicated during the preoperative period in order to achieve downstaging, downsizing, and to reduce the risk of recurrence.

Oncological treatment has a negative impact on the overall physical and mental condition of patients; their quality of life and daily activities are reduced (1). Neoadjuvant therapy is associated with a reduction in cardiopulmonary function among patients undergoing oesophagectomy (2). The decline in cardiorespiratory reserve following neoadjuvant chemotherapy in individuals with oesophagogastric cancer is observed to persist up to the time of surgery (3, 4). The surgical procedures performed are both demanding and prolonged, imposing a significant burden on patients. Furthermore, the duration of surgery correlates with a statistically significant increased risk of complications, including wound infection, dehiscence, hemorrhage, and pneumonia (5).

In the traditional care model, most patients receive rehabilitation in the postoperative period. The rehabilitation aims to improve overall physical fitness, regain self-care abilities, and return to activities patients were able to do before the oncological diagnosis, including returning to their profession and hobbies. One of the main aim of early rehabilitation in postoperative time is to improve the mobility of the patient. Mobilization soon after surgery has a positive effect on recovery of function and therefore it is a part of ERAS (Enhanced Recovery After Surgery) programmes (6). ERAS is becoming a standard part of clinical practice, positively contribute to reducing the risk of postoperative complications, and shortening the length of stay (7–9). Despite the positive effect of ERAS measures, especially the surgery of the upper gastrointestinal tract, is still associated with a high morbidity and mortality. Cardiopulmonary fitness and muscle strength are reduced in these patients; they suffer from fatigue, anxiety, depression, and have lower quality of life (1, 10–14). These accompanying problems negatively influence the therapeutic process, and therefore, lately, attention and efforts to improve postoperative outcomes are increasingly focusing on the period before surgery.

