## Methods

This is a feasibility study focused on patients with oesophagogastric cancer or rectal cancer who were, based on the decision of the multidisciplinary team (MDT) of the University Hospital in Ostrava (FNO), indicated for neoadjuvant therapy in the preoperative period.

These groups of patients were chosen as they are commonly treated with neoadjuvant treatment, which opens a time window for the application of a prehabilitation programme. The prehabilitation programme is designed in the form of physical training aimed at improving or retaining cardiorespiratory fitness as well as the strength of selected muscle groups. Each patient also receives nutritional support. The programme is designed to minimise significant time demands on medical staff, so it will be implemented in the patient's home environment. The study aims to answer question whether the selected patients will be able to complete a home exercise regimen during the preoperative period when they undergo neoadjuvant therapy.

The primary outcomes to evaluate the feasibility of the study are:
1.Percentage of patients who consent to participate in the study out of all diagnosed and for neoadjuvant therapy indicated patients in the monitored period. The reasons for refusing to participate will be recorded.2.The percentage of patients who consent to participate in the study and who remain participants until the end of the study period, out of all consented patients.3.Individual patient compliance—defined as the number of days the patient wore a smart bracelet, carried out or attempted to complete the prescribed exercise programme (aerobic exercise and strength training), and remained accessible for follow-up telephone contact, out of the total number of days in the observed period.4.All adverse events related to the prehabilitation programme implementation.

Secondary outcomes include changes in physical fitness parameters obtained from cardiopulmonary exercise testing CPET—peak oxygen uptake, anaerobic threshold test performed on a Bicycle ergometer ERGOSELECT 5 (Ergoline GmbH, Bitz, Germany and COSMED srl, Rome, Italy) using a ramp protocol with a gradual increase in load of 0.5 W per kilo per min, changes in grip strength measured by hand dynamometer, changes in body composition, Borg's scale of perceived exertion, changes in health-related quality of life measured by EORTC QLQ-C30 quality of life questionnaire, and a subjective perception of the exercise programme.

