## Statistical methods

The collected data will be entered into electronic forms. Basic descriptions of individual groups will be made using descriptive statistical methods. Continuous normally distributed variables will be presented as mean and standard deviation, skewed continuous variables and ordinal variables as median and interquartile range. Categorical data will be presented as numbers and percentages. Demographic characteristics will be compared between groups using a *t*-test or a Mann-Whitney U test (age) and a chi-square or Fisher's exact test (gender). Normality of data will be assessed by a Shapiro-Wilk test. Primary outcomes will be reported as numbers and percentages. To determine the significance of changes during the monitored period, for metric data (peak oxygen uptake, anaerobic threshold, number of steps, grip strength), depending on their distribution, a paired *t*-test or a paired Wilcoxon test will be used. The paired Wilcoxon test will also be used for ordinal data (scores from questionnaires). Comparisons between two diagnostic patient groups for continuous data, again depending on the properties of their distribution, will be performed using a two-sample *t*-test or a Mann-Whitney U test, and for ordinal data, a Mann-Whitney U test. *P*-values less than 0.05 will be considered statistically significant. Statistical analyses will be performed using the IBM® SPSS® Statistics version 28 (IBM, Armonk, USA).

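### Fitness change in a single trained group is judged only by paired tests against zero; report net change with a 95% CI instead, labelled as not an estimate of programme effect

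*Protocol article*

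**What the plan says.** The abstract fixes the design: "This is a single group study design, with all patients enrolled receiving the intervention". The only between-group comparison is oesophagogastric against rectal cancer, and both groups are trained.

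Cardiopulmonary exercise testing (CPET) and grip strength are measured before neoadjuvant therapy starts (Prehabilitation programme) and again in the 1–2 weeks before surgery (Termination of the prehabilitation programme). The interval therefore spans the whole of therapy.

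For the change over that interval, the Statistical methods section reads "To determine the significance of changes during the monitored period, for metric data (peak oxygen uptake, anaerobic threshold, number of steps, grip strength", and continues: "depending on their distribution, a paired *t*-test or a paired Wilcoxon test will be used". The threshold is 0.05. The section names no interval estimate for the change.

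Two statements elsewhere bear on how such a test can be read:
- The Introduction reports that "Neoadjuvant therapy is associated with a reduction in cardiopulmonary function among patients undergoing oesophagectomy", and adds: "The decline in cardiorespiratory reserve following neoadjuvant chemotherapy in individuals with oesophagogastric cancer is observed to persist up to the time of surgery".
- The Methods section describes the programme as "physical training aimed at improving or retaining cardiorespiratory fitness".

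**The concern.** A paired test asks whether the mean (or typical) change differs from zero. With everyone trained, that change is the sum of what therapy does and what training does, and the test sees only the sum. The document itself says that therapy lowers cardiopulmonary function in oesophagogastric patients and that the loss lasts to surgery. For those patients and those measures, zero is not what a useless programme would produce.

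Retention, which is half of the programme's stated aim, coincides with the null hypothesis of the planned test. Failing to reject that null does not show retention, and rejecting it downwards does not show that the programme failed. What is at stake is the message carried into the controlled studies that this one is meant to inform: a p-value against zero gives them neither a size nor a precision.

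**Working it through.** **The plan's own figure.** The only stated figure is the sample size of 40, set on feasibility grounds. The document gives no SD, effect size, expected decline or number of completed pairs, so there is nothing to reproduce. All sizes below are assumptions chosen to show scale.

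**Step 1: what the test can see.** Let D be the therapy effect and P the programme effect, both in units of the SD of within-patient change. The expected change is D + P. The chance of significance comes from the noncentral t distribution with n − 1 degrees of freedom and noncentrality (D + P) × √n, two-sided at 0.05 (sidedness is not stated; two-sided is assumed). Results for 40 pairs, the best case with no dropout:

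| D | P | Net | Significant fall | Not significant |
|---|---|---|---|---|
| 0 | 0 | 0 | 2.5% | 95% |
| −0.5 | +0.5 | 0 | 2.5% | 95% |
| −0.25 | 0 | −0.25 | 34% | 66% |
| −0.5 | +0.25 | −0.25 | 34% | 66% |
| −0.75 | +0.25 | −0.5 | 87% | 13% |

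Rows 1 and 2 cannot be told apart: a programme that fully offsets a half-SD decline looks the same as no effect of anything. Rows 3 and 4 cannot be told apart either: no benefit looks the same as a real benefit that halves the decline.

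**Step 2: a non-significant result is weak evidence of retention.** A true net loss of 0.25 SD is non-significant in 66% of trials with 40 pairs and 81% with 20. The smallest observed mean change that reaches significance is t(0.975, n − 1)/√n:
- 40 pairs: 2.023/6.325 = 0.32 SD
- 20 pairs: 2.093/4.472 = 0.47 SD

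**Step 3: what an interval would show, for peak oxygen uptake.** Half-width = t(0.975, n − 1) × SD/√n. The SD of 2–4 mL/kg/min and the numbers of pairs (30 overall, 15 per diagnosis) are assumed.

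| Pairs | SD 2 | SD 4 |
|---|---|---|
| 30 | 2.045 × 2/5.477 = 0.75 | 2.045 × 4/5.477 = 1.49 |
| 15 | 2.145 × 2/3.873 = 1.11 | 2.145 × 4/3.873 = 2.22 |

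An observed change of exactly zero would leave losses up to the half-width unexcluded. An observed fall just short of significance would leave losses of nearly twice the half-width unexcluded: about 1.5–3.0 mL/kg/min for 30 pairs (2 × 0.75 to 2 × 1.49). Both results would be non-significant. The interval tells them apart; the verdict at 0.05 does not.

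**Step 4: how often a helpful programme shows a significant fall.** Suppose therapy costs 2 mL/kg/min and the programme returns 1, so the net is −1 (assumed). A significant fall then occurs in about 75% of trials with 30 pairs and SD 2, 26% with 30 pairs and SD 4, 44% with 15 pairs and SD 2, and 15% with 15 pairs and SD 4. It can happen, but is not assured.

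**The case against.** The strongest reply is that the plan asks nothing that the test fails to answer. The Statistical methods section speaks only of the significance of changes, and the secondary outcomes are listed as changes. Net change over the preoperative period is a legitimate quantity, and a paired test is a correct test of it. Improving or retaining fitness describes the purpose of the training; it is not a hypothesis or success criterion. The research question is whether patients can complete the regimen. Fitness is secondary, the single-group design is disclosed, and later controlled studies are foreseen. All of this stands, and it confines the point to interpretation and reporting.

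Three stronger readings are tempting, and the documents do not support them:
- **That the authors will present the p-value as the programme's effect or as preserved fitness.** No section says so. What can be said is that nothing guards against it: the limitations in the Conclusion section do not mention the missing control.
- **That zero is the wrong reference throughout.** The persistent decline is stated for cardiorespiratory reserve in oesophagogastric cancer. For rectal patients the Introduction gives only a general statement that oncological treatment harms physical condition, and it states no therapy-related fall in grip strength. The point that non-significance is not retention does apply to both groups and to all three measures.
- **That a programme which halves the decline would be reported as a significant deterioration.** Under the assumptions in step 4 that happens in about 15% to 75% of trials.

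It can also be said that intervals and interpretive wording are often left to a separate analysis plan. That is fair as to detail. The point here concerns the method that the article does fix, a 0.05 criterion for change.

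**Conclusion.** The point holds as a limit on interpretation with a cheap remedy. The planned paired tests are valid for net change, but they cannot separate training from therapy. For CPET measures in oesophagogastric patients, the document's own background makes zero an unsuitable benchmark for the programme. A non-significant result must not be read as retention, nor a significant fall as programme failure. The primary feasibility aim is untouched.

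The logic rests only on the documents. The sizes rest on assumed SDs, declines, programme effects and numbers of pairs. Change in step count is tested in the same sentence but is left out of this point, because steps are the prescribed training dose.

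**What to change.** - In Statistical methods, make the mean (or median) within-patient change with its 95% CI, by diagnosis, the main result for peak oxygen uptake, anaerobic threshold and grip strength, in place of the 0.05 criterion.
- In Statistical methods and in the Conclusion section, state that uncontrolled change combines therapy and training, is not an estimate of programme effect, and serves to plan the later controlled study, for which the size and SD of the change are the useful outputs.
- A formal retention margin is optional and not part of this fix; the document offers no basis for choosing one.

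The cost is wording: no new data, visits or patients. The downside is that no significance claim can be made for the secondary fitness outcomes, and that the intervals within each diagnosis will be wide. The interval does not separate therapy from training either; it shows how much net loss the data can exclude.

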**Methods:**

This is an interventional feasibility study of a prehabilitation programme in the form of physical training conducted at home. The training consists of progressively dosed walking and strength exercises for selected muscle groups. Data will be monitored telemetrically and also through telephone contact with participants. Primary outcomes include: the percentage of patients interested in participating in the study out of all patients indicated for neoadjuvant therapy at University Hospital Ostrava during the observed period, the percentage of patients who complete the prehabilitation programme until the date of surgery and individual patient compliance. Secondary outcomes include physical fitness parameters obtained from cardiopulmonary exercise testing, grip strength measured by a dynamometer, changes in body composition, EORTC QLQ-C30 quality of life questionnaire, and a questionnaire on the subjective perception of the exercise programme. Both primary and secondary outcomes will be compared between study arms (two diagnostic groups). The study is registered at ClinicalTrials.gov, ID: NCT05646043.

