Inclusion criteria for this study are age >18 years and planned resection for locally advanced oesophagogastric adenocarcinoma or adenocarcinoma of rectum with planned neoadjuvant therapy and ability to complete CPET and able to sign informed consent for study participation. Exclusion criteria for this study are contraindications to CPET or inability to perform CPET or daily exercises due to orthopaedic limitations (e.g., amputation, severe gonarthrosis, coxarthrosis) or inoperability determined by the MDT decision or synchronous malignant disease or multivisceral resection or planned non-surgical therapeutic procedures.

The sample size was set at 40 patients given the feasibility nature of the study (34). The patient will be referred to oncologist once MDT agrees on the therapeutic plan. The oncologist, overseeing the oncological treatment, will inform the patient about the possibility of participating in the study and if patient agrees to participate in the study, informed consent will be signed before start of the neoadjuvant therapy.

The length of the prehabilitation programme is based on the length of oncological treatment which for group of patients with oesophagogastric adenocarcinoma consists of four cycles of neoadjuvant chemotherapy at 15-day intervals for a total length of 60 days. The restaging time takes 14–21 days, and time from restaging to surgery usually takes 7–14 days. The total duration for the prehabilitation programme for this group of patients will be about 11 to 13 weeks. For rectal adenocarcinoma, the oncological treatment involves 4–5 weeks of chemo(radio)therapy, followed by restaging after a 3–4 week interval and followed by surgery 1–2 weeks later. The total duration of the programme for this diagnostic group will be around 8 to 11 weeks (Figure 1).

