### Physical training

Physical training will consist of endurance (walking) and strength components. Walking is the most natural physical activity for humans. The training programme aims to be individualised by the research team. The basis for determining the number of steps per day is the baseline value for each patient. This will be increased by 10%–15% every week until the date of surgery. If the increase is not tolerated by the patient, the last increased step count will be retained, and consideration of further increase will be postponed until the following week. The expected total increase in steps is 120%–180% of the baseline. The authors are aware that not every patient can achieve these values. Within the feasibility study, the authors want to verify the acceptable dosing of the load. At the same time, authors' goal is for the patient to perceive their load at medium intensity (measured by the Borg scale, corresponding to 3–4 out of 10) for 30 min per day.

Strength training will be applied using exercises to strengthen the upper (biceps and triceps groups through exercises without and with dumbbels or rubber expander, wall push ups) and lower limbs (strengthening of gluteal, quadriceps, hamstrings and culf muscles through squats with or without back support, standing up from a chair, toe raises, leg raises) and the core. Training will involve a set of eight exercises in several difficulty variations. The patient chooses a variant that he or she can perform and gradually can choose a more difficult variant of the exercise. Each exercise will be done for one minute. The set will be repeated twice. The total strength training time will take approximately 20 min. The patient will perform this set seven days a week. Achievement of Borg 3–4 for strength training is not required. A description of each exercise and photo documentation is part of the exercise diary. The patient is also taught about possible mistakes when performing each exercise and the mistakes are photo documented. The education in the training program is part of the first clinical examination.

If interested, the patient can undertake additional activities (running, cycling, etc.) during the study. Patients will be encouraged to do these activities, and these will be recorded.

Patients will record their daily physical activity in their exercise diaries (number of steps per day, strength training, subjective perception of intensity according to Borg, other physical activities).

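### Step gain is compared between diagnoses without allowing for programme length, although the oesophagogastric programme is longer by design and so has more weekly step increases

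*Protocol article*

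**What the plan says.** All references are to the Protocol article.

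- **Between-group test (Statistical methods).** "Comparisons between two diagnostic patient groups for continuous data, again depending on the properties of their distribution" are made by two-sample t-test or Mann-Whitney U test, with p below 0.05 called significant. No covariate, duration term, per-week scaling or common time point is given, and the comparisons are not labelled exploratory.
- **Variables (Statistical methods).** The sentence on change over the monitored period names its variables: "for metric data (peak oxygen uptake, anaerobic threshold, number of steps, grip strength".
- **Scope (Abstract, Methods).** "Both primary and secondary outcomes will be compared between study arms (two diagnostic groups".
- **Length (Methods).** For oesophagogastric adenocarcinoma: "The total duration for the prehabilitation programme for this group of patients will be about 11 to 13 weeks". For rectal adenocarcinoma: "The total duration of the programme for this diagnostic group will be around 8 to 11 weeks". The difference follows from the oncological treatment.
- **Step rule (Physical training).** One rule serves both groups: "This will be increased by 10%–15% every week until the date of surgery". It is softened by a tolerance clause: "If the increase is not tolerated by the patient, the last increased step count will be retained". One expectation is given for everyone: "The expected total increase in steps is 120%–180% of the baseline".
- **End of training.** The step rule runs up to the day of surgery. The end of the Physical training section and the section on termination of the programme both stop exercise 1–2 weeks earlier.

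**The concern.** A start-to-end step gain accumulates over weekly increments. If the two diagnoses progress at the same weekly rate, the group with more weeks ends with the larger gain. An unadjusted test of that gain then picks up the calendar of the oncological pathway as well as any difference in how patients cope with the programme.

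The groups are not randomised, and they differ in treatment as well as in length. A small p-value for step gain could be taken to mean that one diagnosis responds better to home training when both followed the prescription equally well. The article intends the results to inform larger controlled studies, so this comparison should not carry a difference that the schedule itself creates.

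**Working it through.** **Inputs from the article.** Programme length is 11–13 weeks (midpoint 12) for oesophagogastric and 8–11 weeks (midpoint 9.5) for rectal cancer. The weekly rate is 10%–15% in both groups. The expected total increase is 120%–180%. The total sample is 40 and the significance level 0.05.

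**Assumptions, because the article gives no figure.** Two-sided test; 20/20 split, with 10/30 as a check; SD of the percentage step gain of 30 to 80 points.

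**Step 1: the lengths.**
- Rectal: 4+3+1 = 8 and 5+4+2 = 11 weeks, as stated.
- Oesophagogastric: 60+14+7 = 81 days = 11.6 weeks, and 60+21+14 = 95 days = 13.6 weeks, slightly above the stated range. The stated range is used below; the component sum would widen the gap a little.

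**Step 2: reproduce the expected increase.** Additive reading: gain = weekly rate × weeks.
- 10% × 12 = 120% and 15% × 12 = 180%, exactly the stated range.
- Compounding, (1 + rate)^12 − 1, gives 214% and 435%, which does not match.

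The additive reading is therefore used. Twelve weeks is the oesophagogastric midpoint and lies outside the rectal range.

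**Step 3: same rule, each length, full progression.**

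| Weeks | At 10% per week | At 15% per week |
|---|---|---|
| 8 | 80% | 120% |
| 9.5 (rectal midpoint) | 95% | 142.5% |
| 11 (ranges meet) | 110% | 165% |
| 12 (oesophagogastric midpoint) | 120% | 180% |
| 13 | 130% | 195% |

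Midpoint to midpoint, the gap is 120 − 95 = 25 points at 10% and 180 − 142.5 = 37.5 points at 15%. Taking the same number of weeks off both programmes, for the baseline week and the stop before surgery, leaves it unchanged: with 2 weeks off, 100 − 75 = 25 and 150 − 112.5 = 37.5.

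**Step 4: chance of p<0.05 from length alone.** Two-sample t-test on 38 degrees of freedom, critical value 2.024, noncentrality = gap / (SD × √(1/n₁ + 1/n₂)). Example: 25 / (40 × √(1/20 + 1/20)) = 1.98, which gives 49%.

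| SD of gain | Gap 25, 20/20 | Gap 37.5, 20/20 | Gap 25, 10/30 | Gap 37.5, 10/30 |
|---|---|---|---|---|
| 30 | 73% | 97% | 60% | 92% |
| 40 | 49% | 82% | 38% | 71% |
| 60 | 25% | 49% | 20% | 38% |
| 80 | 16% | 30% | 13% | 24% |

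Every entry exceeds the nominal 5%.

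**Step 5: effect of rescaling.** Per week, 120/12 = 95/9.5 = 10 and 180/12 = 142.5/9.5 = 15, so the additive gap disappears.

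**The case against.** **Steps are not in the outcome list.** The Abstract and Methods do not name number of steps as a primary or secondary outcome. In the Statistical methods it appears by name only in the within-patient sentence. This is fair: that step gain is compared between diagnoses is an inference. It is the natural one, since steps are listed there as metric data and the next comparison covers continuous data without exception.

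**The gap is an average under full progression.** The two length ranges meet at 11 weeks, where the gap is zero. The tolerance clause holds the step count when an increase is not tolerated, the article accepts that not everyone will reach the expected values, and patients help set the next week's load. All this stands and can shrink the gap. A reader might set 8 weeks against 12 and report 40–60 points, but that pairs the rectal minimum with the oesophagogastric midpoint.

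**Other outcomes.** A reader might infer that every between-diagnosis comparison is distorted by length. The article does not support that. Individual compliance is already a share of observed days. Exercise-test, grip and questionnaire changes are not driven by a weekly increment. The aim is to improve or retain fitness, and the Introduction describes decline under neoadjuvant therapy, so even the direction of a length effect is unknown.

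**Power and missing detail.** Low power is not a fault here: 40 was chosen for feasibility and no power is claimed. The handling of incomplete pairs and the test for percentages are details that an article may leave to the full plan.

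**Comparing programmes as delivered is legitimate.** Length belongs to each pathway, and the article nowhere says that a p-value will be read as an effect of diagnosis. As description this is right. It does not fit a significance threshold with no statement of what a difference would mean.

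**Conclusion.** The point holds for step gain. Programme lengths that differ by design, combined with one weekly progression rule, build in a difference of about 25–37.5 percentage points between the diagnoses, midpoint to midpoint, if increases are tolerated equally. With a 20/20 split and an SD of 30–80 points, an unadjusted test would fall below 0.05 in about 16%–97% of trials from length alone. The direction follows from the article's own figures. The size rests on the additive reading, equal tolerance, and the assumed split and SD. It does not extend to compliance, exercise testing, grip strength or the questionnaires.

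**What to change.** 1. Compare step gain between diagnoses at a common training week that every planned programme reaches, or as change per training week, using the weekly step data already collected. Per-week change removes the gap only if increments are additive. Under compounding, 147.3/9.5 = 15.5 against 213.8/12 = 17.8 points per week at the 10% rate, so a difference would remain. The common week does not depend on that reading. It must be chosen with care: stopping 1–2 weeks before surgery leaves 6–7 training weeks of an 8-week programme, or 5–6 if the baseline week falls inside it, so week 7 can come after training has ended.
2. Report the difference with a 95% CI and label all between-diagnosis comparisons exploratory, because the groups are not randomised and differ in treatment and programme length. Adding length as a covariate is a weak substitute, since diagnosis largely determines it.
3. Reconcile the step rule that runs to the date of surgery with the two places that end training 1–2 weeks before. They set the training length on which either comparison depends.

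Cost: a few sentences in the analysis plan and slightly more analysis, with no new data. The price is that no significance claim is made between diagnoses.
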